**10.3.2 Analysis of the Primary and Secondary** **Efficacies**

For the primary and secondary outcomes, covariance analysis will be used to compare differences in mean changes from baseline between groups, with group as a factor and baseline value as a covariate. A step-down approach will be used to find a significant result; the primary and secondary outcomes were tested sequentially to control the familywise type I error rate according to the following order: mean changes in the number of HIV tests at six months (primary outcome), mean changes in the number of HIV tests at three months, mean changes in the sexual partner number at six months, and mean changes in the frequency of condomless sex at six months. Statistical significance (two-sided P<0.05) at each step was required to test the next hypothesis. A linear mixed-effects model with individuals as a random effect will be used to evaluate the main effects of the intervention and interaction effects of time on the primary outcome.

**10.3.3 Other analysis of the primary intervention effect**

Subgroup analyses for the primary outcome will be performed based on age, education, occupation, income, marital status, and transient population. For sensitivity analysis, the results with imputation will be presented.

**10.4 Sample Size Considerations**

We used PASS V. 15.0 (NCSS, LLC. Kaysville, Utah, USA) to calculate the sample size based on a repeated measures design with two time points. Enrolment of 103 participants per group was projected to provided 90% power to detect a mean difference of 0.35 in the number of HIV tests per three months^1^ between groups (two-tailed α = 0.05). At least 115 patients per group were needed, assuming an anticipated 10% dropout rate.

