**10.4.2 Summary Statements**

Group sample sizes of 103 and 103 achieve 90% power to detect a difference of 0.35 in a design with 2 repeated measurements having a Compound Symmetry covariance structure when the standard deviation is 1, the correlation between observations on the same subject is 0.2, and the alpha level is 0.05.

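### The stated 90% power belongs to an average of two measurements per person; read as written, the gatekeeping month-6 ANCOVA has about 73%, and the primary time window is not defined consistently

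*Protocol*

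**What the plan says.** **Sample size.** Section 10.4, repeated in the synopsis, states that enrolling 103 per group "was projected to provided 90% power to detect a mean difference of 0.35 in the number of HIV tests", expressed as a rate over three months and tested two-sided at 0.05. Section 10.4.2 describes two repeated measurements with compound symmetry and gives the inputs: "when the standard deviation is 1, the correlation between observations on the same subject is 0.2, and the alpha level is 0.05". The table in 10.4.1 reports an actual power of 0.90019 by the normal approximation. A 10% dropout allowance raises 103 to at least 115 per group.

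**Primary test.** Section 10.3.2 plans an ANCOVA of the change from baseline, with treatment group as the factor and the baseline count as the covariate. The first hypothesis in the step-down order is "mean changes in the number of HIV tests at six months (primary outcome"). The change in test number at three months is a separate second step. Each step must reach two-sided P<0.05 before the next is tested. The synopsis gives the same method and order. Both places also plan a linear mixed model for the primary outcome, but it has no place in the testing order.

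**Time window.** The primary objective (synopsis and section 1.1) and the primary outcome (synopsis and section 10.3.1) refer to the change during, not at, six months of follow-up. The effect size is expressed per three months. Item B2 in Appendix C asks for the number of tests in the previous three months only. Surveys are at baseline, month 3 and month 6. Nowhere does the protocol say that the two follow-up counts are summed or averaged.

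**The concern.** The sample-size calculation gains precision by averaging two measurements per person. The ANCOVA in the testing order, taken as written, uses one follow-up count per person plus the baseline count. At a correlation of 0.2, the baseline covariate removes very little variance, whereas a second follow-up measurement removes a lot. The two are not interchangeable, so the 90% describes a different comparison from the one that decides the trial.

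The primary test is also the gate. If it misses significance, the three-month test count, partner number and condomless sex cannot be formally tested. Under the month-6 reading, the chance of missing a true difference of 0.35 would be about 27% rather than 10%.

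**Working it through.** **Inputs (sections 10.4 to 10.4.3):** n = 103 per group, difference d = 0.35 tests per three months, standard deviation of a single observation 1, within-person correlation ρ = 0.2, two time points, compound symmetry, two-sided alpha 0.05, normal approximation.

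**Formulas.** With V the variance per person of the quantity compared:
- power = Φ(d / √(2V/n) − 1.960)
- n per group for 90% power = 2(1.960 + 1.2816)² V / d²

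**1. The protocol's own figure.** The mean of two measurements has V = (1 + 0.2)/2 = 0.60.
- n = 2 × 10.508 × 0.60 / 0.1225 = 102.9, so 103.
- Standard error = √(1.20/103) = 0.1079; 0.35/0.1079 = 3.243; power = Φ(1.283) = 0.9002.

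This matches the 0.90019 in section 10.4.1. Dropout: 103/0.9 = 114.4, so 115. The stated figures are correct for that model.

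**2. ANCOVA of the month-6 count.** With baseline as covariate, V = 1 − r², where r is the baseline-to-month-6 correlation. Using the change from baseline as the response gives the same group comparison once baseline is in the model. At r = 0.2, V = 0.96.
- Standard error = √(1.92/103) = 0.1365; 0.35/0.1365 = 2.564; power = Φ(0.604) = 0.727.
- With all 115 per group and no dropout: 0.773.
- Detectable difference at 90% power: 3.2416 × 0.1365 = 0.44.
- n for 90% power: 2 × 10.508 × 0.96 / 0.1225 = 164.7, so 165 evaluable per group (165/0.9 = 183.3, so 184 with 10% dropout).

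**3. Sensitivity to r.** The protocol gives no correlation specifically for baseline with month 6, so the range is an assumption. Power at 103 per group:

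| r | V | Power |
| --- | --- | --- |
| 0 | 1.00 | 0.709 |
| 0.2 | 0.96 | 0.727 |
| 0.3 | 0.91 | 0.750 |
| 0.4 | 0.84 | 0.782 |
| 0.5 | 0.75 | 0.826 |

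Reaching 90% needs V of about 0.60, so r = √0.40, about 0.63.

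**4. If both follow-up windows are combined,** with a difference of 0.35 in each and ρ = 0.2 throughout:
- Total of the two counts, unadjusted: difference 0.70, V = 2(1 + 0.2) = 2.4; 0.70/√(4.8/103) = 3.243; power 0.900.
- Average of the two counts, adjusted for baseline: V = 0.60 − 0.2² = 0.56; 0.35/√(1.12/103) = 3.357; power 0.919.

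**The case against.** The strongest reply is that the month-6 reading is not settled. The objective and the outcome definition speak of the change during six months, and the protocol uses during and at loosely: partner number is described one way in section 10.3.1 and the other way in 10.3.2. An effect expressed per three months would suit a rate over both windows, and on that reading power is 90% to 92%. This stands as a real ambiguity and makes the 73% conditional. It does not remove the point: the testing order names six months and three months as separate hypotheses, the questionnaire recalls three months only, and no text combines the two surveys.

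Second, ρ = 0.2 is the correlation between the two modelled time points, and section 10.4 does not say which two they are. Section 10.4.1 defines it generally, as the correlation between observations on the same person, so using it for baseline and month 6 is reasonable but is an extrapolation. That is why a range belongs beside the 73%. The whole range from 0 to 0.5 stays below 90%.

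Third, the mixed model resembles the sample-size model. However, it sits outside the step-down order, and the protocol states neither a baseline covariate nor a contrast averaged over time for it.

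A reader might infer that the sample-size arithmetic is wrong, or that the trial is underpowered at 73% whatever was intended. The documents support neither. The calculation reproduces, and the shortfall depends on how the primary window is read. Nor does lower power bias the estimate or raise the type I error.

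**Conclusion.** The concern holds in conditional form. The 90% in section 10.4 and the synopsis is the power of a comparison averaged over two measurements. The first test in the step-down order, as worded, is an ANCOVA at six months. For that test, power at 103 evaluable per group is about 73%, or 71% to 83% over assumed baseline correlations of 0 to 0.5, with a detectable difference of about 0.44 at 90% power. This assumes a month-6 difference of 0.35, a standard deviation of 1 and one three-month count per person. The 90% is right only if the primary outcome is the average or total over both windows, which the testing order does not say. As written, the power statement and the deciding test do not match.

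**What to change.** Define the primary time window once, in the same words in the synopsis (objective, primary outcome and analysis) and in sections 1.1, 10.3.1 and 10.3.2, and state the power of the matching test.

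- **If the month-6 ANCOVA stays primary:** restate the power in section 10.4 and the synopsis as about 73% (71% to 83% for baseline correlations of 0 to 0.5), with a detectable difference of about 0.44 at 90%. The cost is wording and a less favourable stated power.
- **If the average or total over months 3 and 6 was intended:** say so, and make the baseline-adjusted contrast averaged over both times the first test in the step-down order, specifying the covariate and the contrast. Power is then about 90% to 92% at 103 per group, without extra participants or data. Note that this primary test would share its month-3 data with the second step. This is a choice of estimand, not just an edit: adopt it before outcome data are reviewed by group.

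Either revision goes to the Ethics Committee under section 12.2.

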**10.4.1 Tests for Two Means in a Repeated Measures Design in PASS**

Two-Sided Test. Null Hypothesis: D = 0. Alternative Hypothesis: D ≠ 0.

Covariance Type = Compound Symmetry

| Target Power | Actual Power* | N1 | N2 | N | **M** | **D1** | **Sigma** | Rho | Alpha |
| --- | --- | --- | --- | --- | --- | --- | --- | --- | --- |
| 0·90 | 0.90019 | 103 | 103 | 206 | 2 | 0.35 | 1 | 0.2 | 0·05 |

* Power was computed using the normal approximation method.

Note: Target Power is the desired power value (or values) entered in the procedure. Power is the probability of rejecting a false null hypothesis.

Actual Power is the power obtained in this scenario. Because N1 and N2 are discrete, this value is often (slightly) larger than the target power.

N1 and N2 are the number of items sampled from each population.

N is the total sample size, N1 + N2.

M is the number of time points (repeated measurements) at which each subject is observed.

D1 is the difference between the means of groups 1 and 2 under the alternative hypothesis.

Sigma is the standard deviation of a single observation. It is the same for both groups. Rho is the correlation between observations on the same subject.

Alpha is the probability of rejecting a true null hypothesis.

**10.4.2 Summary Statements**

Group sample sizes of 103 and 103 achieve 90% power to detect a difference of 0.35 in a design with 2 repeated measurements having a Compound Symmetry covariance structure when the standard deviation is 1, the correlation between observations on the same subject is 0.2, and the alpha level is 0.05.

**10.4.3 Parameter setting**

| Parameter | Setting |
| --- | --- |
| Alternative Hypothesis: | Two-Sided |
| Power: | 0.90 |
| Alpha: | 0.05 |
| Group Allocation: | Equal (N1 = N2) |
| D1 (Difference\|H1) | 0.35 |
| M (Number of Time Points) | 2 |
| Covariance Type: | Compound Symmetry |
| Sigma (Std Dev of a Single Observation) | 1 |
| Rho (Autocorrelation) | 0.2 |

**11. QUALITY CONTROL**

**11.1 Design Phase of the Protocol**

- Before the formal commencement of the study, a small-scale pre-survey will be conducted to refine personnel recruitment and inclusion, as well as improve the survey questionnaire.
- Training will be provided to the relevant staff members to ensure the quality of the research work.

**11.2 Implementation Phase of the Protocol**

- Strictly adhere to the inclusion criteria for survey participants and conduct rigorous screening and recruitment.
- Use a unique identification number to ensure the unique identity of recruited participants.
- Provide educational campaigns on HIV self-testing (HIVST) related knowledge to the TG individuals participating in the study. Ensure feedback rates and result authenticity by obtaining informed consent, providing reminders via phone or SMS, and offering a certain level of financial compensation.
- Minimize loss to follow-up during the survey process as much as possible.

**11.3 Analysis Phrase of Data**

Two survey personnel will be assigned to independently conduct data cleaning and data logic checks (e.g., range checks for data values). Any discrepancies will be resolved by third survey personnel.

**12. ETHICS**

**12.1 Informed Consent**

The investigator needs to provide a digital informed consent form. Before participants can take part in the study, the investigator must obtain the participant's informed consent in digital form after fully explaining the purpose, methods, anticipated benefits, and potential risks of the research. The participants should sign the digital informed consent form before any interventions take place. The digital informed consent form should be personally signed and dated by the participant. If a potential participant is illiterate or has impaired vision and does not have a legally acceptable representative, the investigator must provide an impartial witness to read the informed consent form to the participant and allow for questions. Subsequently, the participant and the witness must sign the informed consent form to demonstrate that the informed consent was given voluntarily and understood.

**12.2 Institutional Review Board/Independent Ethics Committee**

The protocol was developed prior to the start of the study. The plan was jointly discussed and signed by the researchers and the team leader, and it was submitted for approval to the Ethics Committee before implementation. If any issues arise during the implementation of this plan, the research protocol should be revised, and the revised protocol should also be submitted for approval to the Ethics Committee. Prior to the commencement of the study, researchers must provide participants with relevant details of the study, including the study content, objectives, potential benefits and risks, as well as the rights and obligations of the participants. During the study, all personal information of the participants will be kept strictly confidential.

**12.3 Confidentiality**

Restrict staff who have access to the personal information of participants and sign confidentiality agreements. Participants' personal information should be stored in locked cabinets at the workplace and supervised by designated personnel. CBO staff members should apply in advance for contact information before accessing participants' contact details, and use dedicated phones within the cabinets to communicate with participants. In all materials submitted to the project lead organization and the ethics committee, only the participants' and their partners' identification codes should be recorded.

The researchers unanimously agree that all information obtained from the project lead organization during the study is the property of the project lead, including manuals, agreements, and all other information related to the study. This information shall not be disclosed to any third party, except for individuals or institutions directly involved in this study or as required by law.

**13. DATA PROCESSING AND STORAGE**

**13.1 Database Establishment**

Statisticians should promptly establish a database, and after reviewing the database, investigators, statisticians, and research assistants will lock the data. To ensure data security, unauthorized personnel are not allowed to modify the data, and data must be backed up.

**13.2 Data Storage**

Investigators should ensure the integrity of the data. According to the principles of the Chinese “Guideline for Good Clinical Practice (GCP),” research data should be retained for at least five years.

**13.3 Data Availability**

All data from the study will be provided to the corresponding author, who has the ultimate authority to make decisions regarding the data.

**14. TIMELINE OF STUDY PLAN**

We plan to complete the initial participant recruitment and questionnaire design between June 2020 and September 2020. The preliminary survey and questionnaire revisions will be completed from October 2020 to December 2020. From January 2021 to December 2021, we aim to complete participant recruitment and a six-month follow-up. Data analysis is expected to be completed before March 2022.

**15. ROLE OF THE FUNDING SOURCE**

The study is to be funded by National Natural Science Foundation of China (82073620), and the Liaoning Revitalization Talents Program (XLYCYSZX1904). The funder of the study will have no role in the study design, data collection, analysis, interpretation, or writing of the manuscript.

**16. DECLARATION OF INTERESTS**

The principal investigators of the overall trial and each study site have no financial interests or other competing interests.

**Appendix B. Screening questionnaire**

S01. Your age is (in years). [fill in the blank]

S02. Your assigned sex at birth was？ (Single choice)

- Male
- Female

S03. How do you identify your current gender? (Single choice)

- Male
- Female
- Transgender female
- Intersex
- Uncertain

S04. Which of the following gender-affirming surgeries have you undergone? (Multiple selections allowed)

- No (Exclusive options)
- Breast augmentation
- Male genital and gonadal removal, female genital reconstruction
- Adam's apple reduction
- Facial feminization
- Other

**Appendix C. Online questionnaire (partly)**

Welcome to participate in the questionnaire survey for the Transgender Women's Health Promotion Project. This research project has been reviewed by the Ethics Committee of the First Affiliated Hospital of China Medical University. Your participation in this project will be beneficial for you to understand your own HIV and STI infection status, and it will also provide us with an opportunity to grasp the HIV and STI epidemic among the transgender community in our country, enabling us to better provide health services for everyone. This survey is anonymous, and we solemnly promise to strictly protect your personal privacy. We hope that you can truthfully complete the survey. Thank you sincerely for your participation!

**What is your PID? [fill in the blank]**

**Part A. Demographic Characteristics**

A1. What is your ethnicity? [Single choice]

- Han
- Manchu
- Tibetan
- Mongolian
- Uyghur
- Others

A2. What is your highest level of education? (Single choice)

- No formal education
- Primary school
- Junior high school
- Senior high school or vocational school
- Associate degree
- Bachelor's degree
- Master's degree or above

A3. What is your current occupation? (Single choice)

- Student
- Unemployed
- Employed with a stable job
- Sex worker/Entertainer
- Other: **________________________________________**

A4. What is your current average monthly income?

[fill in the blank] (Chinese Yuan)

A5. What is your current marital status? [Single choice]

- Single
- Cohabitation
- Living with a homosexual partner
- Living with a heterosexual partner
- Married
- Widowed

A6. What type(s) of medical insurance do you have? (Select one or more)

- None
- Employee Basic Medical Insurance
- New Rural Cooperative Medical Insurance
- Urban Resident Basic Medical Insurance
- Commercial Medical Insurance (purchased directly from insurance company)

A7. Who do you currently live with? (Single choice)

- Living alone
- Wife or female partner
- Male partner
- Parents/siblings/relatives
- Friends (roommates)/colleagues (co-renting)
- Dormitory (provided by school/workplace)
- Other

**Part B. HIV Testing Behavior**

B1. Have you been tested for the HIV in the past three months? (Single choice)

- Yes
- No

B2. How many times have you been tested for the HIV in the past three months? [fill in the blank]

B3. Have you participated in venue-based (VCT/hospital/CBO workgroup) HIV testing in the past three months? (Single choice)

- Yes
- No

B4. How many times have you been tested for venue-based HIV in the past three months? [fill in the blank]

B5. Have you used HIV self-testing (HIVST) for HIV testing in the past three months? (Single choice)

- Yes
- No

B6. How many times have you used HIVST for HIV testing in the past three months? [fill in the blank]

B7. Have you shared HIVST with your sexual partners in the past three months? (Single choice)

- Yes
- No

B8. In the past three months, which type of sexual partners have you shared HIVST with? (Single choice)

- Regular male sexual partner (i.e., boyfriend or male partner in a stable relationship for at least three months)
- Casual male sexual partner (i.e., non-commercial and non-transactional)
- Commercial male sexual partner (i.e., engaging in sexual activities with male partners in exchange for goods, money, or housing)
- Female sexual partner

B8. How many times have you shared HIV self-testing (HIVST) with your regular sexual partner in the past three months? [fill in the blank]

B9. How many times has your regular sexual partner been tested for HIV in the past three months? [fill in the blank]

B10. In the past three months, are you aware of the HIV infection status of your regular sexual partner? (Single choice)

- HIV negative
- HIV positive
- Not aware

B11. How many times have you shared HIVST with your casual sexual partner in the past three months? [fill in the blank]

B12. How many times has your casual sexual partner been tested for HIV in the past three months? [fill in the blank]

B13. In the past three months, are you aware of the HIV infection status of your casual sexual partner? (Single choice)

- HIV negative
- HIV positive
- Not aware

B14. How many times have you shared HIV self-testing (HIVST) with your commercial sexual partner in the past three months? [fill in the blank]

B15. How many times has your commercial sexual partner been tested for HIV in the past three months? [fill in the blank]

B16. In the past three months, are you aware of the HIV infection status of your commercial sexual partner? (Single choice)

- HIV negative
- HIV positive
- Not aware

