**Secondary Efficacy Outcomes:**

- The mean changes in the number of HIV tests during three months of follow-up.
- The proportion of HIV testing at six months.
- The proportion of HIV testing at three months.
- The mean changes in partner numbers during six months of follow-up.
- The mean changes in the frequency of condomless sex during six months of follow-up.

**Study Design:** This study is an open-label, randomized controlled trial. Eligible participants for screening are HIV-negative TGW. The minimum expected total recruitment of TGW is approximately 230, with a minimum expected recruitment of approximately 115 participants in the intervention group and the control group.

**Sample Size:** We used PASS V. 15.0 (NCSS, LLC. Kaysville, Utah, USA) to calculate the sample size based on a repeated measures design with two time points. Enrolment of 103 participants per group was projected to provided 90% power to detect a mean difference of 0.35 in the number of HIV tests per three months^1^ between groups (two-tailed α = 0.05). At least 115 patients per group were needed assuming an anticipated 10% dropout rate.

**Summary of Participants Eligibility Criteria:** The following are inclusion criteria for candidates: being 18-65 years of age, assigned male at birth and self-identifying as female, no previous record of HIV positive test results, tested negative for HIV antibodies in the rapid test during the screening, engaged in sexual activity in the past six months, willing to provide truthful information about their sexual behaviour, own a smartphone and able to use WeChat, and provide electronic informed consent. The following are the exclusion criteria for candidates: candidates who do not meet the defined inclusion criteria, encompassed a positive HIV status prior to enrolment and refusal to partake in the study.

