**4.1 Inclusion and Exclusion Criteria**

**4.1.1 Inclusion Criteria**

- Aged 18 to 65 years old.
- Assigned male at birth, and self-identifying as female.
- Tested negative for HIV antibodies during the screening at enrolment.
- Engaged in sexual activity in the past six months.
- Willing to provide truthful feedback on their sexual behaviour.
- Owns a smartphone and is able to use WeChat.
- Willing to sign an informed consent form.

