**6. PARTICIPANTS ENROLLMENT**

Before initiating specific research activities/procedures, all participants must personally sign the digital informed consent form. Each participant has been assigned a unique identification number, which will be used throughout the study to identify the individual and must be used in all research-related documents pertaining to that participant. This identification number must remain unchanged throughout the study; it should not be altered, including during re-screening of participants, after the initial assignment.

**Confirmation of TGW identity:** The study participants' transgender female identity is verified through a logical screening process using self-identified gender questions in the baseline questionnaire. Researchers rigorously assess the identity of the participants. If there are doubts about the identity of a participant, an additional identity confirmation questionnaire is sent, which includes questions about transgender-related knowledge. Additionally, the following methods are used to corroborate their identity: contacting the participant's recruiter to request identity verification evidence, reviewing the participant's social media posts for identity-related clues or evidence, and requesting the participant to provide recent photos of themselves presenting in feminine attire.

When the researchers determine that a participant meets the inclusion criteria, the investigator should record this decision and the date in the digital Case Report Form (CRF).

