**7. STUDY PROCEDURES**

**7.1 Baseline**

Eligible participants will undergo an online informed consent process. After agreeing to participate in the study, participants will be invited to complete a questionnaire survey. The demographic and behavioural characteristics of the two groups of participants will be collected through an online survey platform (<https://jinshuju.net/home>).

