**7.2 Follow Up**

For all participants, the study duration is six months from enrolment. All participants will receive follow-up surveys based on the online questionnaire platform at three and six months after enrolment.

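### The HIV testing items do not exclude the trial's own screening test, which can dilute the three-month testing proportion and blur baseline counts, though it does not bias the primary comparison

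*Protocol*

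**What the plan says.** **The trial's own test.** Protocol 4.1.1 requires of every participant: "Tested negative for HIV antibodies during the screening at enrolment". The eligibility summary in the Synopsis names the method: "tested negative for HIV antibodies in the rapid test during the screening".

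**The testing items.** Appendix C, Part B, opens with "Have you been tested for the HIV in the past three months" (B1) and "How many times have you been tested for the HIV in the past three months" (B2). B3 to B6 repeat the pair for venue-based testing and for self-testing. As printed, none of the six excludes the screening test. Section 10.3.1 relies on participants' reports and states no exclusion either.

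**Order of test and baseline questionnaire.** Section 7.1 reads: "Eligible participants will undergo an online informed consent process. After agreeing to participate in the study, participants will be invited to complete a questionnaire survey". Taken alone, this puts the test first. Section 6, however, verifies transgender identity, itself an inclusion criterion, by "using self-identified gender questions in the baseline questionnaire". Section 4 requires consent before any research procedure. Section 7.4 fixes only that a negative test comes before randomisation.

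**Follow-up.** Section 7.2 places the surveys "at three and six months after enrolment".

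**Use in the analysis.** Section 10.3.2 compares mean changes from baseline by ANCOVA, with group as factor and the baseline value as covariate. The step-down sequence holds test counts at six and three months, partner number and condomless sex. The testing proportions at three and six months are secondary outcomes but are not in that sequence.

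**The concern.** The trial wants to measure how often participants test in the course of their lives. A test taken only to enter the study is not that behaviour, yet the items as worded can count it.

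It can enter at two points:

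- **Baseline.** If the screening test comes first and items are answered literally, B1 is yes and B2 is at least 1 for everyone. The baseline count is both the reference for change and the ANCOVA covariate.
- **Month 3.** Three months back from the month-3 survey is roughly the enrolment date, so some respondents may report the screening test there.

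The yes/no outcome is the more exposed. One extra test turns an untested respondent into a tested one but leaves an already tested one unchanged. Even when both arms count alike, the arms are drawn together. Once the answers are in, an analyst cannot reliably tell who counted the study test.

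**Working it through.** **Step 1: the plan's own figure.** Inputs from Protocol 10.4 to 10.4.3: difference 0.35, SD 1, two time points, correlation 0.2, two-sided alpha 0.05, power 90%.

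- Variance of the mean of two measures: (1 + 0.2)/2 = 0.6.
- n per group = 2 × 0.6 × (1.960 + 1.282)² / 0.35² = 102.9, so 103. Power at 103 is 0.9002.
- With 10% dropout: 103/0.9 = 114.4, so 115.

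The stated size is reproduced, and this point does not change it.

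**Step 2: three-month proportion.** Let p be the true proportion tested apart from the study test, and f the share who count the study test at month 3. Assume f is the same in both arms and unrelated to other testing.

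- Observed proportion = f + (1 − f)p.
- Observed arm difference = (1 − f) × true difference.

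The protocol gives neither f nor arm-specific proportions. For illustration only, take 34.6% in the control arm (the testing figure for China in section 2, which has no recall period) and an assumed 20-point gain, with 103 per group:

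| f | Control | Intervention | Difference | Power |
|---|---|---|---|---|
| 0 | 34.6% | 54.6% | 20 points | 83% |
| 0.25 | 50.9% | 65.9% | 15 points | 59% |
| 0.5 | 67.3% | 77.3% | 10 points | 36% |
| 0.75 | 83.7% | 88.7% | 5 points | 18% |
| 1 | 100% | 100% | 0 | no comparison |

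**Step 3: counts, bias.** If everyone adds 1 at baseline, the covariate shifts by a constant and the group coefficient is unchanged. If only some do, the addition is made before randomisation and is unrelated to arm. The ANCOVA was simulated with assumed overdispersed counts (control mean 0.6, true difference 0.35, 103 per arm, 2,000 runs):

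| Share counting at baseline / at follow-up | Estimated difference | Power | Control-arm change |
|---|---|---|---|
| 0 / 0 | 0.348 | 64% | 0.00 |
| 1 / 0 | 0.350 | 64% | −1.01 |
| 1 / 1 | 0.349 | 64% | 0.00 |
| 0.5 / 0.5 | 0.346 | 53% | 0.00 |
| 1 / 0.5 | 0.344 | 54% | −0.50 |

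The between-arm estimate holds throughout. The within-arm change can move by a full test. The 64% reflects the assumed counts and is not a check of the plan's 90%.

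**Step 4: counts, precision.** Apply the protocol's SD of 1 and correlation of 0.2 to baseline and follow-up (an assumption). Uneven counting adds variance f(1 − f), at most 0.25 when half count.

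- No counting: residual variance 1 − 0.2² = 0.960.
- Half count at baseline only: 1 − 0.04/1.25 = 0.968, up 0.8%.
- Half count at baseline and at month 3: 0.968 + 0.25 = 1.218, up 27%.

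The precision loss therefore falls almost wholly on the three-month count. A six-month count taken from the month-6 item is reached only through the baseline covariate, and there the loss is very small.

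**The case against.** The strongest reply has four parts.

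- **The order is not fixed.** If the questionnaire is completed before the test, baseline is clean. This stands. A reader might infer that everyone necessarily scores as tested at baseline, but sections 4, 6, 7.1 and 7.4 together do not establish it. An open order is no protection either: if it varies between participants, counting becomes uneven.
- **The primary comparison is safe.** This also stands. One might set the possible extra baseline test against the target difference of 0.35 and infer a threat to the treatment effect. That compares a shift common to both arms with a difference between arms, and the ANCOVA effect does not move.
- **The month-3 ceiling is a worst case.** Agreed. The test was taken at or before enrolment, so a survey answered on time or late would often leave it outside the window. The month-6 window excludes it. The three-month proportion is outside the step-down sequence, so no confirmatory claim rests on it.
- **The text is incomplete.** Appendix C is marked as partial, no separate follow-up form is printed, and sections 11.1 and 14 plan a pre-survey and questionnaire revision. An instruction could exist elsewhere. But Part B shows B1 to B6 in sequence without one, and sections 7.6 and 10.3.1 add none. An analysis plan could not repair this later, because the answers would not show who counted the test.

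**Conclusion.** The point holds as a defect of item wording with limited reach.

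- **Three-month testing proportion:** the arm difference shrinks by (1 − f), from no dilution at f = 0 to complete loss at f = 1. The value of f is unknown. The result assumes that the month-3 survey reuses the printed items and that both arms count alike.
- **Test counts, including the primary outcome:** the between-arm difference is unbiased, because the test precedes randomisation and applies to both arms. For the three-month count this again needs equal counting in the two arms. Uneven counting costs precision, chiefly at month 3.
- **Within-arm changes from baseline:** these can be distorted by up to one test per person, if all count the test at baseline and none later. Control-arm testing would then seem to have fallen.
- **Six-month proportion:** unaffected when read from the month-6 item.

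Neither the sample size nor the planned analysis needs to change. The case for acting is that the remedy is nearly free and must be in place before data are collected.

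**What to change.** 1. Add to items B1 to B6, at baseline and month 3: *Do not count the test you took to join this study.*
2. State the same exclusion in the outcome definition in Protocol 10.3.1.
3. State in sections 6 and 7.1 whether the baseline questionnaire is completed before or after the screening test.
4. Keep the fixed three-month recall window, and at month 3 count only tests after the enrolment date. Do not anchor the month-6 items to the month-3 survey: that is undefined for anyone who missed it and gives windows of unequal length.

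The cost is slightly longer wording in six items on two survey forms, plus short additions to three protocol sections.
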